| Early Postoperative Complications/Adverse Events (within 30 days postoperatively) | | Confirm the presence of adverse events through medical history and physical examination.  If an adverse event occurs, document the event name, onset time, outcome, severity (including whether reoperation was required), relationship to cervical spine surgery, treatment details/date of treatment, and whether hospitalization was extended. | |
| Medical History/Physical Examination | | Conduct medical history and physical examination during regular postoperative outpatient visits. | |
| Plain X-ray | | Cervical spine (AP/Lateral/Anterior flexion lateral/Posterior flexion lateral): Confirm C2-7 angle/C-SVA/C7 slope  Full spine standing (AP/Lateral): Confirm SVA/Lumbar lordosis angle/Thoracic kyphosis angle/Pelvic incidence, check for existing vertebral fractures | |
| Cervical Plain CT | | Horizontal, sagittal, and coronal slices at each intervertebral level: Confirm presence of OPLL/Lamina retention rate, hinge fractures/gutter bone union. | |
| Cervical Plain MRI | | T2 and T1 sagittal/horizontal images  Preoperative: Maximum stenosis level, presence of intramedullary signal changes, C4/5 paraspinal muscle area, dural sac area  Postoperative: C4/5 paraspinal muscle area, dural sac area, Grading of the mass posterior to the dural sac | |
| Late Postoperative Complications/Adverse Events (From 31 days post-op to within 2 years post-op) | | If an adverse event occurs, document: event name, onset timing, severity, outcome, seriousness (whether reoperation required), relationship to cervical spine surgery, treatment details/date, and hospitalization status. | |
| Outcome Investigation | | Survival (Last confirmed survival date, presence/absence of death, date of death, cause of death)  Reoperation (Reoperation presence/absence, reoperation date, reason for reoperation, reoperation method)  Study Discontinuation (Discontinuation presence/absence, discontinuation date, reason for discontinuation) | |
| Direct Medical Costs | | Hospitalization Costs (Medical fees excluding surgery, surgery-related costs [surgery, surgical drugs, anesthesia, anesthetic drugs])  Outpatient Costs (Consultations, tests, drugs, other)  Hospitalization Re-treatment Costs for Adverse Events (Hospitalization medical fees excluding surgery, surgery-related costs [surgery, surgical drugs, anesthesia, anesthetic drugs])  Research collaborators collect the above costs from medical claims. | |

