**7.4** **Instructions for Research Participants**

The principal (sub-investigator) investigator shall provide the following instructions to research participants before the study begins.

1) Advise participants that when visiting other departments or hospitals, they must inform the attending surgeon or pharmacist of their participation in the study and, whenever possible, consult with their attending surgeon beforehand.

If prior consultation is not possible, instruct them to report to their attending surgeon afterward.

2) Advise participants that if they experience any physical discomfort, they should promptly report it to their attending surgeon and consult about the need for medical care.

3) Instruct participants not to disclose information about this clinical research on social media or similar platforms.

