**＜Secondary Endpoints＞**

(1) Operative Time

(2) Estimated Blood loss

[Definition]

Operating time is defined as the time recorded in the anesthesia record.

Blood loss is defined as the amount recorded in the anesthesia log. If “minor bleeding” is recorded, it is considered 10 ml of blood loss.

(3) Proportion achieving the MCID in cervical JOA score recovery rate at postoperative 1 and 2 years

[Definition]

Refer to the description under <Primary Evaluation Items> for the definition of JOA score recovery rate.

Following previous reports19), the MCID for JOA score recovery rate is set at 52.8%. The MCID achievement rate at 1 year and 2 years postoperatively is evaluated for each group.

(4)　 Health-related QOL (EQ-5D) at postoperative 1 and 2 years

[Definition]

Obtained via patient self-completion of the Japanese-language questionnaire (attached separately). If the patient cannot complete the questionnaire due to writing difficulties caused by cervical myelopathy, family members or healthcare professionals will assist with completion.

Health-related QOL will be assessed using the EQ-5D before surgery, postoperative 1 year, and 2 years. Note: The EQ-5D is also used as the utility value when calculating the incremental cost-effectiveness ratio (11).

(5) Severity of neck pain, upper limb pain, and upper limb numbness (VAS) at postoperative 1 and 2 years

[Definition]

Obtained through the patient's own completion of a questionnaire form created in Japanese (attached separately). If the patient cannot complete the questionnaire due to writing difficulties caused by cervical myelopathy, a family member or healthcare professional will assist with completion.

The severity of pain and numbness will be assessed using a 0–100 mm VAS before surgery and at postoperative 1 and 2 years.

(6) Neck disability index (NDI) at postoperative 1 and 2 years compared to preoperative

[Definition]

Data is collected via the Japanese version questionnaire (attached separately) completed by the patient themselves. If the patient cannot complete the questionnaire due to writing difficulties caused by cervical myelopathy, family members or healthcare professionals will assist with completion.

Health-related QOL due to cervical spine disease is assessed before surgery, and postoperative 1 year and 2 years using the NDI total score.

[figure not shown]
(7) Retention rate of enlarged lamina at postoperative 1 and 2 years (Retention rate)

[Definition]

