Collect direct medical costs at the facility where surgery was performed for each patient at discharge, and at 1 and 2 years post-surgery. Direct medical costs include inpatient treatment costs and outpatient treatment costs for the following services, summing ①, ②, and ③.

① Inpatient treatment costs for DCM surgery (surgery-related costs [surgery, surgical drugs, anesthesia, anesthetic drugs]), excluding surgical fees

② Outpatient costs for DCM after the surgery date (consultations, tests, drugs, other)

③ Rehospitalization costs for adverse events (inpatient treatment fees excluding surgery, surgery-related costs [surgery, surgical drugs, anesthesia, anesthetic drugs])

The cost-effectiveness evaluation metric uses the Incremental Cost-Effectiveness Ratio (ICER). The ICER is calculated by subtracting the control group's costs from the trial treatment group's costs. (ICER). ICER is calculated by dividing the incremental cost—the difference between the trial treatment group's costs and the control group's costs—by the incremental effect—the difference between the trial treatment group's effect and the control group's effect.

The outcome measure used is QALY (quality-adjusted life year). QALY is calculated using a Markov model that accounts for patients requiring reoperation or experiencing death, based on QOL measured by EQ-5D. Utility values and cost values are discounted annually at a rate of 2%, as recommended by the Central Social Insurance Medical Council (https://c2h.niph.go.jp/tools/guideline/guideline_ja.pdf).

(15) Surgical complication incidence

Surgical complications are categorized into intraoperative, early postoperative (within 30 days after surgery completion [wound closure]), and late postoperative (from day 31 after surgery up to 2 years postoperatively) complication rates.

Mortality (all deaths during the study period) and reoperation rate within 2 years postoperatively are recorded independently for complications.

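### ICER costs stop at the operating hospital while QALYs and the reoperation rate have no such limit; the resulting bias is probably small and of unknown direction

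*Protocol*

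**What the plan says.** **Cost side.** Protocol 8.2 (14) instructs: "Collect direct medical costs at the facility where surgery was performed for each patient at discharge", and again at 1 and 2 years. It then sums three components under that rule: ① inpatient costs of the index surgery, ② later outpatient costs for DCM, and ③ "Rehospitalization costs for adverse events". Section 7.2.2 gives the source: "Research collaborators collect the above costs from medical claims". No other-hospital source is named, and no rule covers care given elsewhere.

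**Effect side.** In the same item, "QALY is calculated using a Markov model that accounts for patients requiring reoperation or experiencing death". The utilities come from the patient: "Health-related QOL will be assessed using the EQ-5D before surgery, postoperative 1 year, and 2 years". Section 7.2.2 (Outcome Investigation) records "Reoperation (Reoperation presence/absence, reoperation date, reason for reoperation, reoperation method", and 8.1.2 (15) reports a reoperation rate within 2 years and all deaths. None of these is limited by facility, and the treating facility is not a listed item.

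**Outside care.** Section 7.4 tells participants that "when visiting other departments or hospitals, they must inform the attending surgeon", with prior consultation where possible and a report afterwards otherwise.

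**Weight of the endpoint.** The rationale for endpoint (14) in section 5.1 treats superior cost-effectiveness of the anchor as a key objective of the study.

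**The concern.** The two parts of the ratio cover different sets of events. A reoperation at the operating hospital enters ③ at its claimed cost. The same reoperation at another hospital enters at zero, yet its effect on the patient's EQ-5D at 1 and 2 years is still measured and, if the site learns of it, the Markov model can count it. The cost of failure is therefore understated in whichever arm has more failures, readmissions or transfers treated elsewhere.

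This matters because the case for the anchor rests on price, and fixation failure is one of the safety questions on which the two methods are compared. A cost rule that loses part of the price of failure acts on the quantity the economic analysis is meant to settle.

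**Working it through.** The protocol states no expected cost, QALY difference or ICER, so there is no figure of its own to reproduce. The check is a comparison of the text followed by an illustration of size.

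**1. What each side counts for an off-site reoperation, as written**

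| Element | Limited to operating hospital? | Off-site reoperation counted? |
|---|---|---|
| Cost ③ (readmission) | Yes, 8.2 (14) | No |
| Cost ② (DCM outpatient) | Yes, 8.2 (14) | Only later visits back at the operating hospital |
| EQ-5D at 1 and 2 years | No limit stated | Yes, if completed |
| Markov reoperation and death | No limit stated | Yes, if learned of |
| 2-year reoperation rate | No limit stated | Yes, if learned of |

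**2. Inputs for size**

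- Fixation failure (section 3.2): anchor 1.8-5.5% (reclosure); plate 3.4-13.3% (screw loosening or dislodgement). Used as a stand-in for reoperation.
- Implant price (section 3.2): plate 506,700 yen for three laminae, anchor 138,000 yen for two. Gap = 506,700 - 138,000 = 368,700 yen.
- Assumed, not in the protocol: 50% of events treated elsewhere; 1,500,000 yen per event.

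**3. Formula**

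Change in the anchor-minus-plate cost difference when the omitted cost is restored = unit cost × share elsewhere × (anchor rate - plate rate). Here unit cost × share = 1,500,000 × 0.5 = 750,000 yen. A negative result means that the plan as written understates the anchor's saving; a positive one means that it overstates it.

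| Anchor rate | Plate rate | Change (yen per patient) | Relative to 368,700 |
|---|---|---|---|
| 1.8% | 13.3% | 750,000 × (-0.115) = -86,250 | 23.4% |
| 5.5% | 13.3% | 750,000 × (-0.078) = -58,500 | 15.9% |
| 3.65% (midpoint) | 8.35% (midpoint) | 750,000 × (-0.047) = -35,250 | 9.6% |
| 1.8% | 3.4% | 750,000 × (-0.016) = -12,000 | 3.3% |
| 5.5% | 3.4% | 750,000 × 0.021 = +15,750 | 4.3% |

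**4. Sensitivity to the assumptions**

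With 10% treated elsewhere and 727,800 yen per event (the laminoplasty fee in section 3.2), the extremes shrink to 72,780 × (-0.115) = -8,370 yen and 72,780 × 0.021 = +1,528 yen.

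**5. Sign**

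The change is positive only where the anchor rate exceeds the plate rate. Within the quoted ranges this needs a plate rate between 3.4% and 5.5% and an anchor rate above it. Elsewhere the change is zero or negative.

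**The case against.** The strongest reply has five parts.

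- **Silence on place is not inclusion.** This stands in part. A reader might infer that reoperations are counted wherever they happen. The protocol does not say so; it only sets no limit. Section 7.4 is a general instruction that may bring some patients back to the operating site. An off-site reoperation enters the event count only if the site hears of it.
- **The care may not be free in the ICER.** A reader might infer that an off-site failure costs nothing at all. That goes too far, since later DCM visits at the operating hospital fall under ②. A Markov reoperation state could carry an average cost, and 8.2 (14) does discount costs alongside utilities. But the text uses the model for QALYs and defines cost as the sum of ① to ③, so a state cost would be an addition to the plan.
- **The bias need not favour the anchor.** This stands. The anchor arm alone gives 5.5% × 50% × 1,500,000 = 41,250 yen, about 11% of the price gap, which could be read as an overstated saving. An ICER uses a difference, and the plate range is higher, so most of the range points the other way. Nor is 727,800 yen a valid minimum per missed reoperation: section 3.2 gives it for five laminae, and the managements in Table B of 8.2 include lesser procedures that the protocol does not price.
- **This belongs in the SAP.** Unit-costing detail does. The facility limit does not: it is a rule stated in the protocol, which an analyst following the plan would apply.
- **Single-hospital claims are a feasible choice.** True, and the remedy keeps them as the main source.

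**Conclusion.** The mismatch is real as written: costs end at the operating hospital's door, while the measured health effect and the reoperation count do not. It is a modest flaw in one secondary endpoint.

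The illustrated range of about -86,000 to +16,000 yen per patient rests on three things: failure rates standing in for reoperation rates, half of the events treated elsewhere, and 1.5 million yen each. The last two have no basis in the protocol, and not every failure leads to a reoperation, so these are upper illustrations. The implant gap is itself a rough yardstick, because it compares three plated laminae with two anchored ones.

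A reader might infer that the omission could reverse the cost ranking or that it flatters the anchor. Neither is supported. The largest shift against the anchor is about 4% of the implant gap, and the direction is unknown. The non-inferiority analysis of the JOA recovery rate uses no cost data and is untouched.

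**What to change.** 1. In 7.2.2, add a treating-facility field to the reoperation record and to the adverse-event records.
2. In 8.2 (14), state that each reoperation or adverse-event readmission at another hospital is costed at the insurance fee schedule, or at the trial's mean cost for the same type of event. Apply the same rule in both arms and add the amount to ③.
3. Report the operating-hospital-only total as a sensitivity analysis.

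The cost is one data field and one analysis rule. No outside claims and no extra staff are needed. The unit costs will be approximate, and the rule works only for off-site events learned of at follow-up, so the 1- and 2-year outcome investigation should ask about them explicitly. Setting the rule before data are seen also keeps the choice of unit cost from being made once the distribution of events by arm is known.

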## **3.2 Standard Treatment for Target Diseases**

Surgical treatment for DCM has developed primarily in Japan, as mentioned above, due to its high prevalence among Asians. Extensive laminectomy was commonly performed in the 1970s and 1980s. However, issues such as postoperative progression of cervical kyphosis and recurrence of spinal cord symptoms due to posterior dural scarring after laminectomy were noted. Consequently, in the late 1980s, Japanese surgeons developed cervical laminoplasty as a posterior approach technique. Two techniques for cervical laminoplasty have been proposed: the open-door technique^4)^ and the double-door technique^5)^ (Figure 2).

[figure not shown]

Reports indicate no difference in postoperative outcomes between the unilateral and bilateral approaches, establishing laminaoplasty as the standard treatment for DCM without kyphotic deformity or anterior compression^6)^.

Problems associated with the bilateral laminoplasty approach include reported worsening of myelopathy due to reclosure of the enlarged lamina and cervical kyphosis^7,8)^. Therefore, to prevent reclosure of the enlarged lamina, the suture-anchor method (Fig. 3 left)^9-11)^ and the lamina spacer method (Fig. 3 center)^12-15)^ were developed. In recent years, the mini-plate method (Fig. 3 right)^16-18)^ has become widespread.

[figure not shown]

|  | Suture-Anchor | Laminar Spacer | Mini-plate |
| --- | --- | --- | --- |
| reclosure of enlarged laminae | 1.8-5.5% | 2.9-21.3%  (Spacer dislodgement rate) | 3.4-13.3%  (Screw dislodgement rate) |
| JOA score recovery rate | 42.4-59.8% | 43.2-52.3％ | 47.1-83.4% |
| Technical complexity | Simple | Complex | Simple |
| Cost (material fee) | Low  138,000yen／2 laminae | low  120,800 yen／4 laminae | High  506,700 yen／３laminae |
| Surgical Fee (Medical Fee) | 727,800 yen／5 laminae | | |

　　　※JOA score：Japanese Orthopaedic Association score

The suture anchor method has also reported favorable surgical outcomes with JOA score recovery rates of 42.4-59.8%^9-11)^. On the other hand, the plate method has been reported to offer the advantages of a simpler surgical procedure and superior fixation strength^16-18)^. However, no high-quality randomized controlled trials have been conducted to determine whether the plate method yields superior surgical outcomes compared to the conventional suture anchor method, and no conclusion has been reached.

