Furthermore, even with the plate method, reclosure of the enlarged lamina due to screw loosening has been reported in 3.4-13.3% of cases. No comparative studies including safety aspects have been reported to date to determine whether the plate method is safer than the suture anchor method, which has a lamina reclosure rate of 1.8-5.5%.

While the surgical fees for the three methods are the same, material costs differ significantly. Under Japan's insurance reimbursement system, the plate method costs ¥506,700 for use on three laminae, which is higher than the ¥138,000 for the suture anchor method used on two laminae. To date, no cost-effectiveness analysis has been conducted, and the benefits of using the more expensive plate method remain unclear.

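### The ICER costs the index admission by a different rule from readmissions and from the collection list, and no list says whether implant material counts

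*Protocol*

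**What the plan says.** Section 8.2(14) of the protocol adds three cost items. Item ① covers the index admission: "Inpatient treatment costs for DCM surgery (surgery-related costs [surgery, surgical drugs, anesthesia, anesthetic drugs]), excluding surgical fees". Item ② covers outpatient care. Item ③ covers readmission: "Rehospitalization costs for adverse events (inpatient treatment fees excluding surgery, surgery-related costs [surgery, surgical drugs, anesthesia, anesthetic drugs", with no exclusion of surgical fees.

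The collection list in section 7.2.2 is built like item ③: "Hospitalization Costs (Medical fees excluding surgery, surgery-related costs [surgery, surgical drugs, anesthesia, anesthetic drugs". It uses the same construction for readmissions, and the source is given as "Research collaborators collect the above costs from medical claims".

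Section 3.2 keeps two prices apart. Its table has a row headed "Surgical Fee (Medical Fee"), with one value for all methods (727,800 yen for 5 laminae), and a separate row for material cost. The text adds: "While the surgical fees for the three methods are the same, material costs differ significantly". On material, "the plate method costs ¥506,700 for use on three laminae", "which is higher than the ¥138,000 for the suture anchor method used on two laminae".

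The rationale for endpoint (14) in section 5.1 calls cost-effectiveness part of a key objective. For the calculation, section 10.5.3(14) sends the reader to 8.1.2, which gives only the endpoint's name. The definition itself is in 8.2(14).

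**The concern.** Three things do not fit together.

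- Item ① puts surgery among the included costs and removes surgical fees in the same line, without defining either term so that the two can be told apart.
- Item ① has no non-surgical inpatient component. Section 7.2.2 collects one for the index stay, and item ③ counts one for a readmission.
- Drugs and anesthesia are itemised, but implant material is not named in any list. It is the cost difference on which section 3.2 builds the case for the trial.

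At stake is the numerator of the ICER. Two analysts following the text in good faith could cost the same index admission differently, and the choice about material could move the between-arm difference by several hundred thousand yen per patient. The primary endpoint is not affected.

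**Working it through.** The protocol states no incremental cost or ICER, so there is no figure to reproduce. The check compares the lists and then applies the protocol's own prices.

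**Step 1. Components named in each list**

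| Component | 7.2.2, index stay | 8.2(14) item ① | 8.2(14) item ③ |
|---|---|---|---|
| Inpatient fees other than surgery | included | not listed | included |
| Surgery | included | listed, but surgical fees then excluded | included |
| Drugs used at surgery; anesthesia and its drugs | included | included | included |
| Implant material | not named | not named | not named |

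Item ① differs from the other two lists in the first two rows. All three are silent in the last.

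**Step 2. Inputs, from section 3.2**

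- Plate material: 506,700 yen for 3 laminae, so 506,700 / 3 = 168,900 yen per lamina.
- Anchor material: 138,000 yen for 2 laminae, so 138,000 / 2 = 69,000 yen per lamina.
- Surgical fee: 727,800 yen, the same for all methods.

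**Step 3. Index-surgery difference (anchor minus plate), fee and material switched in or out**

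| Fee | Material | Plate (yen) | Anchor (yen) | Difference (yen) |
|---|---|---|---|---|
| out | out | 0 | 0 | 0 |
| out | in | 506,700 | 138,000 | −368,700 |
| in | out | 727,800 | 727,800 | 0 |
| in | in | 1,234,500 | 865,800 | −368,700 |

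The surgical fee cancels. Of these two components, only material moves the difference.

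**Step 4. Range by number of laminae**

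The 368,700 yen sets three plated laminae against two anchored ones. Section 7.1.3 allows 2 to 4 expanded laminae. Assuming that cost is linear per lamina, which the protocol does not state, the gap is k × (168,900 − 69,000) = k × 99,900 yen for k laminae in each arm:

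- 2 v 2: 199,800 yen
- 3 v 3: 299,700 yen
- 4 v 4: 399,600 yen

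Unequal numbers are possible, since 7.1.3 asks for at least two plates or at least two anchors. Four plated laminae against two anchored would give 4 × 168,900 − 138,000 = 537,600 yen.

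**The case against.** The strongest reply is that item ① is a translation slip. If the excluding phrase has drifted from the inpatient fees to the end of the line, item ① matches 7.2.2 and item ③. The neighbouring sentence defining the ICER is itself garbled, which makes this plausible. It is still an inference, and it leaves implant material unnamed.

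A reader might go further and infer that item ① removes the device cost. The documents do not support that as the necessary reading. In the terms of section 3.2, the surgical fee is the common 727,800 yen and material is separate. Excluding the fee therefore need not touch implants, which can sit under surgery in the brackets. The device is lost only if surgery is taken to mean the surgical fee, or if the bracketed list is closed and does not cover material.

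Nor does section 3.2 say that material is the only cost that differs. Drugs, anesthesia, outpatient care and readmissions are also costed and may differ between arms.

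Two further points reduce the weight. The costs come from claims, and 7.2.2 collects more than item ① uses, so the data are probably recoverable. Section 3.4 also treats cost-effectiveness as a secondary endpoint, and section 4 sets no separate cost-effectiveness objective. Analysis detail may go to the SAP, but that does not excuse cost lists that already disagree within the protocol.

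**Conclusion.** The point holds as an inconsistency in a stated rule. As written, item ① costs the index admission differently from a readmission and from the collection list, and it is unclear about surgery itself. Whether implant material is counted is undecided; the text does not show that it is left out.

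The open question is worth 368,700 yen per patient on the prices as quoted, or 199,800 to 399,600 yen for equal numbers of laminae under the linear assumption. Reading material as not included would set that contribution to 0. It would not set the whole incremental cost to 0, because the other components remain. The effect of omitting non-surgical inpatient fees cannot be sized, since the protocol gives no figure for them.

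This should be corrected because section 5.1 presents cost-effectiveness as a key objective. It does not bear on the non-inferiority conclusion.

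**What to change.** Use one identical component list in 7.2.2 and in items ① and ③ of 8.2(14): inpatient fees other than surgery, plus surgery-related costs, plus implant material actually used (plates and screws, or anchors).

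State explicitly whether the common surgical fee is in or out. On the protocol's figures it adds nothing to the index-surgery difference, so either choice is workable if it is the same everywhere.

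Correct the pointer in 10.5.3(14) from 8.1.2 to 8.2(14).

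Confirm that the number of implants used can be read from the claims, because the surgical information in 7.2.2 records implant type and size but does not list the number.

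The cost is protocol wording, with no new visit or test. It is best done before cost extraction begins, so that all sites work from the same list.
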